### Practical strategies

Literature was reviewed to identify which strategies are most frequently found as part of successful interventions aimed at increasing (vigorous) physical activity and improving dietary habits. Synergies between diet and exercise in modifying body composition have been reported [48,49]. Furthermore, a combination of interventions on physical activity and dietary habits were found to be more (cost-)effective than interventions on physical activity alone [50].

A review on determinants of participation in worksite health promotion programmes showed that programmes that offer a multi-component strategy and focus on multiple behaviours have a higher overall participation level [51]. When targeting multiple lifestyle behaviours, identifying an individual's stage-of-change on behaviour can help to determine which behaviours an individual should be targeted for change (at various points) in the intervention [52]. The stage-of-change construct can facilitate tailoring of interventions by matching intervention strategies to individuals' motivational readiness. Furthermore, in weight management in which multiple diet and activity changes can achieve weight change, individuals may be more motivated to change some specific behaviours than in others. Therefore, participants should be able to choose which behaviour they intend to change.

A strategy for increasing risk awareness could be feedback on health screening. The review of Soler et al. 2010 [53] indicates that assessment of health risks with feedback is useful as a gateway intervention to a broader worksite health promotion programme that may include a set of health promotion activities to improve the health of employees. The workers indicated in the focus group interviews that there often is no sufficient follow-up or feedback during or after the PHS. Standardised follow-up is available only in the case of high risk (for example high blood pressure). Also, as a preventive measure, feedback and personal information could be very important to induce behaviour change [54,55]. This was also found to be effective in construction workers [56]. Therefore, personal counselling with extra feedback for behaviour change should be an important element of the intervention.

#### Step 4: Producing programme components and materials

In this step of the IM process methods and practical strategies are translated into programme components and materials. The starting point of the intervention should be informing the employees about the company health promotion activities. Personal health coaching and information materials should be added to the current health promoting activities of the company to include all determinants of the formulated programme objectives.

### Programme description

The intervention will take place during a 6-month period and will consist of materials and tailored information on physical activity and diet, personal health coaching (PHC), and training instruction. Both the PHC protocol and specific materials were developed to be able to connect the intervention to the PHS and tailor the intervention to the needs (individual risk factors) and wishes of the participants. Based on the baseline measurements and questionnaires a quick scan will be applied to tailor the intervention to the participants. Tailoring variables will be health indicators (BMI and waist circumference), current lifestyle behaviour (physical activity) and stage-of-change (for physical activity as well as dietary behaviour).

### Programme materials

The programme materials were made attractive and recognisable for the target group by using a standard lay-out and logo. The "VIP in Construction toolbox" will consist of tailored brochures, a calorie guide, a pedometer, a BMI card and waist circumference measuring tape, recipes and a knowledge tests, an overview of the company health promoting facilities, PEP forms, and an exercise card. The exercises will consist of strengthening and stabilization exercises for the abdominal and dorsal muscles and will be well described on an exercise card. The exercises should be performed 3 times a week. The participants will receive instruction for the use of the exercise card from the PHC. The exercises on the card should be easily fitted in daily life routines; participants should be able to perform the exercises at home, and without any use or purchase of materials which potentially enhances compliance.

### PHC

The coaching contacts will specifically aim at the programme outcomes as formulated in the needs assessment. The coaching contacts will consist of the following elements: 1) feedback, 2) goal setting, 3) feedback on formulated goals, 4) instructions for self-monitoring, and 5) training instruction.

1) The participants will receive additional feedback on their health screening and current lifestyle behaviour.

2) The PHC will support in goal setting, by helping the participants in formulating a personal motivation and action plan. These plans will contain physical activities, healthy food choices or a combination. Participants will be encouraged to target behaviour that is not at the desired level. Questions will be asked on what participants want to change, and they will be asked to formulate and write down specific goals and strategies to change the behaviour. In addition, information about the company's health promoting activities will be given and the intervention materials will be distributed and clarified.

3) Feedback on formulated goals will be given during the follow-up contacts. The PHC will keep a record of the goals and plans of the participant; in the follow-up contacts these goals should be evaluated. Possible barriers should be discussed and/or new goals should be formulated.

4) Participants will receive instructions for self-monitoring by using the PEP forms and materials.

5) The PHC will give instructions how to use the exercise card.

During the intervention, participants will be coached face-to-face in formulating their personal motivation and action plan. Follow-up contacts (feedback and motivating) will be conducted by telephone. The number and duration of contacts will vary with the outcome of the quick scan, with a minimum of 2 and a maximum of 4 contacts. The number of contacts (A, B, C) will be determined by a participant's stage-of-change (for physical activity as well as dietary behaviour). An overview of the contacts is given in Table 6. A web-based system will be used to register the participants' appointments, follow-up contacts, and content of the contacts (goals & action plans).

**Table 6 T6:** Coaching contact schedule

PHC contacts	2 weeks after baseline measurements	1 month	2 months	3 months	4 months
A	Intake (60 min face-to-face)	Follow-up 1: (30 min; telephone)	Follow-up 2: (15 min; telephone)		Follow-up 3: (15 min; telephone)

B	Intake (60 min face-to-face)		Follow-up 1: (30 min; telephone)	Follow-up 2: (15 min; telephone)	

C	Intake (30 min face-to-face)			Follow-up 1: (10 min telephone)	

#### Step 5: Adoption & implementation plan

The product of step 5 is a plan for accomplishing programme adoption and implementation by influencing behaviour of individuals who will make decisions about adopting and using the programme and the individuals who deliver the programme.

#### Company involvement

To gain insight into facilitating factors and possible barriers regarding the adoption and implementation, management and (potential) users of the programme were interviewed. The human recourse management was involved in the programme development from the start to ensure top-down adoption in the organisation and increase of the chance of long-term implementation. During the intervention period the process will be monitored for unforeseen difficulties and possible barriers in adoption. Also a communication plan was written for the company. The main goal of this communication plan was to inform the target group and the management about the project and to obtain support from the direct management.

#### Participants' compliance (important factors to encourage the adoption of the intervention by the participants)

To decrease barriers for participation, communication to the participants will be performed in cooperation with their employers, to show company involvement and support for the programme. Furthermore, the invitation to the study will be done simultaneously with the invitation to the PHS, to adapt the programme to the regular procedures. To make participation feasible for the participants the follow-up measurements as well as the first face-to-face contact with the coach will take place at the worksite and during work hours.

In the planning of the programme, the planning of regular health screening was taken into consideration. Based on de schedules of the health screening, it was decided that the recruitment for the intervention should last at least 12 months, to ensure exposure to all the companies' business units, and worker age groups.

The participating occupational physicians (OP) and nurses received instructions during a kick-off meeting as well as by e-mail and telephone, as they will have an important role in linking the intervention to the PHS and motivating the workers to participate. To ensure that a standardized protocol will be used by the PHCs, all coaches received a manual describing the protocol and goals for the coaching sessions in detail. Just before the start of the intervention a training session will be held.

### Phase II evaluation

#### Step 6: Evaluation plan

##### Study design

The effectiveness of the programme will be measured by performing an RCT. Participants will be measured at baseline (T0), at 6 months (T1), and at 12 months (T2). Consenting participants will be randomised to the intervention or control group after the baseline measurement. The control group will receive care as usual and will only be contacted for the baseline and follow-up measurements. The study design and procedures have been approved by the Medical Ethics Committee of the VU University Medical Centre.

##### Study population and setting

The research population will consist of all blue collar workers of a construction company. This will include construction site workers as well as factory workers of the company. The recruitment of participants will be conducted through the usual communication channels of the company at a non-compulsory PHS.

##### Power calculation

Sample size was based on detecting a difference in change in body weight between the intervention and the control group. In each group (intervention and control) 130 participants will be needed, based on a power of 80% and an alpha of 5%, and an expected weight loss of 1.5 kg (sd 4.3 kg) as result of the intervention. The used standard deviation was subtracted from previous work from our research group, studying construction workers [56]. Taking into account a loss to follow-up of 20%, 324 workers should be included in this study.

##### Randomisation

Randomisation will take place at an individual level. After baseline measurements the participant will be randomly assigned to either the intervention or the control group by a computer generated list using SPSS (version 15). The randomisation will be prepared and performed by an independent researcher (i.e. the research assistant).

##### Measurements

Assessment of the study parameters will be done using a combination of questionnaires and physiological measurements. Part of the study parameters will be obtained from physical examinations and questions on outcome measures are based on questions used for the PHS survey in the construction industry. In the Netherlands, this survey is widely used and tested on validity among construction workers who participate in PHS.

Together with the invitation for this company PHS, all workers will receive a brochure about the study, an informed consent form, and an additional questionnaire in order to measure those variables not included in the PHS. For each study parameter, the following paragraphs describe how it will be measured for this study.

### Primary outcome measures

#### Body composition

##### Body weight and BMI

Body weight and height will be measured at the OHS by the occupational physician or the assistant during the PHS. Weight will be measured using a digital weight scale. Body weight and height will be measured with the participants standing without shoes and heavy outer garments. Data on body weight and height will be used to calculate Body Mass Index (BMI) (kg/m^2^).

##### Waist circumference

BMI does not give insight into body fat distribution; therefore waist circumference will be measured as an indicator of health risks associated with visceral obesity [57]. Waist circumference will be measured during the PHS by the OP or assistant as midway between the lower rib margin and the iliac crest with participants in standing position at the end of expiration [58]. To standardize waist circumference measurement, OPs and assistants will be provided with a Seca 201 waist circumference measure (Seca, Hamburg, Germany) and measuring protocol.

### Secondary outcome measures

#### Musculoskeletal disorders (MSD)

The prevalence of MSD will be assessed using questions derived from the PHS. Using a dichotomous scale (yes/no), questions relate to the prevalence of regular pain or stiffness in both the upper and lower extremity regions. Additionally, using the validated Dutch Musculoskeletal Questionnaire [59], the prevalence of MSD during the past three months will be measured for the different body regions. The intensity of pain will be measured using Von Korff scales [60]. Workers will be asked to indicate their intensity of pain (i.e. average pain and worst pain experienced) on an 11-point numerical scale (0-10).

#### Energy balance-related behaviour

##### Physical activity

The frequency of vigorous activities will be obtained from the PHS questionnaire and moderate physical activity will be assessed by the number of days per week moderate intensity activities are performed (such as walking and cycling) for at least 30 minutes. These questions relate to international physical activity guidelines [61] as well as to the Dutch guidelines [62]. Additionally, the validated Short Questionnaire to Assess Health enhancing physical activity (SQUASH) will be applied [63]. The SQUASH measures duration, frequency and intensity of different domains of physical activity (active work transportation, occupational physical activity, household activities, and leisure time activities). Data from the SQUASH will be expressed as energy expenditure in METminutes per week.

As a complementary method, physical activity and sedentary behaviour will be assessed objectively using accelerometers in a random sample of 50 participants of both the intervention (n = 25) and control group (n = 25). This random sample will wear an accelerometer (Actigraph) during 7 consecutive days. The accelerometer will register the actual physical activity during and outside work hours.

##### Dietary intake

Alcohol consumption will be obtained from the PHS questionnaire asking participants to report their average consumption (in glasses per week). Portion size at dinner, number of beverages and slices bread, as well as consumption of energy dense snacks will be assessed using questions that were also used in the Health under Construction study [64]. Average weekly intake and daily portions of several food groups during a usual week during the past month are indicated in these questions. Fruit and vegetable consumption will be measured using the validated Short Fruit and Vegetable questionnaire (validity r = 0.50) [65]. The number of days per week and the number of daily servings of fruit, vegetables and fruit juice will be measured using five items on citrus fruit, other fruits, cooked vegetables, raw vegetables, and fruit juice.

#### Determinants of energy balance-related behaviour

The intervention will aim at improving energy balance-related behaviour (physical activity and dietary behaviour). Personal coaching and feedback will be tailored to self-efficacy and stage-of-change. Therefore, it is necessary to measure these constructs for physical activity and dietary behaviour. Based on models of behaviour and behaviour change, questions will be asked on knowledge, attitudes, self-efficacy and stage-of-change for physical activity and dietary behaviours [46,47].

#### Health-related measures

##### Self-reported Physical Functioning

Subjective physical functioning will be measured using the RAND-36 [66,67]. The RAND-36 health survey is a widely known and reasonably reliable and valid measurement of health-related quality-of-life [68]. The RAND-36 consists of 36 questions, with clusters of: physical functioning, social functioning, role limitations (physical problem), role limitations (emotional problem), mental health, pain, general health perception, and health change. In the present study, the validated Dutch version will be used.

##### Fitness

Although maximal volume of oxygen consumption (VO_2_max) is considered the gold-standard for measuring aerobic capacity, its measurement requires strict protocols and trained personnel. For this study fitness will be measured by using a non-exercise test estimation model including age, BMI, resting heart rate, and self-reported physical activity [69,70].

##### Cardiovascular disease (CVD) risk profile

CVD risk profile will be assessed using the European Systematic Coronary Risk Evaluation (SCORE) [71]. The SCORE is based on the CVD risk variables smoking, systolic blood pressure, and blood cholesterol levels (either total cholesterol or the ratio total/HDL cholesterol). All variables will be measured by the OP or the assistant during the PHS. Blood cholesterol (mmol/l) will be measured by taking a venous blood sample. The SCORE will be filled in based on blood pressure and cholesterol levels, as assessed in the medical examination and smoking behaviour as assessed in the PHS questionnaire.

#### Work-related measures

##### Workplace productivity loss

Sickness absence data (work absenteeism) will be collected from company records. Presenteeism (reduced productivity while at work) will be measured using the WHO Work Performance Questionnaire (WHO-HPQ) [72,73] and the PROductivity and DISease Questionnaire (PRODISQ) [74]. Participants will be asked to complete these questionnaires at 3, 6, 9, and 12 months.

##### Work ability

For companies work ability is an indicator of the productivity of its own human resources. Work ability will be assessed by the Work Ability Index as measured in the PHS questionnaire.

##### Work engagement, work satisfaction & vitality

Vitality will be assessed by the six items of the Utrecht Engagement Scale (UWES) that refer to high levels of energy and resilience, the willingness to invest effort, not being easily fatigued, and persistence in the face of difficulties [75]. In addition, work related measures such as organisational commitment and work satisfaction will be evaluated.

##### Use of company facilities

Since the intervention aims to increase the use of company health promoting facilities (e.g. company sponsored fitness), the use of these facilities will be reported by the participants at 6 and 12 months.

#### Cost measures

##### Intervention costs

These include the costs for the "VIP in Construction toolbox" and the PHC. PHC costs include costs for the health coach, housing costs, costs for printed materials, and travel expenses of the PHC. Since the PHC contacts will take place during work hours, the costs of lost productivity due to the intervention will be included as well. Coaches will record the frequency and duration of the face-to-face and telephone contacts. Intervention costs will be valued using a bottom-up approach.

##### Other workplace health promotion costs

The use of company facilities will be valued using invoices of contractors.

##### Health care costs

These include care by the general practitioner, allied health care, medical specialist, complementary and alternative medicine, hospitalisation, and medications. Data on resource use will be collected at a three monthly basis using retrospective questionnaires. Dutch standard costs will be used to value health care utilization [76]. If these are not available, prices according to professional organizations will be used. Medication use will be valued using unit prices provided by the Dutch Society of Pharmacy [77].

##### Productivity-related costs

Workplace productivity losses (i.e. work absenteeism and presenteeism) will be valued using salaries of the participants when using the employer's perspective and using average salaries per gender and five-year age group when using the societal perspective.

##### Participant costs

Since the intervention stimulates participants to engage in regular physical activity, self-reported costs related to sports activities (membership fees and sports equipment costs) will be collected on a three monthly basis.

#### Effect analysis

The effectiveness of the lifestyle intervention will be assessed using a regression analysis with the outcome measures at follow-up (6 months and 12 months) as the dependent variables and adjusting for the baseline levels of the outcome measure. Both crude and adjusted analyses will be performed. Linear and logistic (longitudinal) regression analyses will be performed using SPSS 18.0 (SPSS Inc. Chicago, Illinois, USA). According to the intention-to-treat principle, all available data of the participants will be used for data analysis. For all analyses, a two-tailed significance level of < 0.05 will be considered statistically significant.

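### Three co-primary outcomes at two follow-ups are all tested at an unadjusted 0.05, while the trial is sized on body weight alone: one primary analysis should be named

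*Protocol article*

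**What the plan says.** All references are to the protocol article.

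- **Primary outcome measures.** Body weight and BMI share one subheading. Waist circumference has its own, with the rationale that BMI does not show fat distribution: "therefore waist circumference will be measured as an indicator of health risks associated with visceral obesity". The section on secondary outcomes starts after these. Economic evaluation also refers to the primary outcomes in the plural.
- **Power calculation.** "Sample size was based on detecting a difference in change in body weight between the intervention and the control group". The inputs are 80% power, alpha 5% and "an expected weight loss of 1.5 kg (sd 4.3 kg) as result of the intervention", and the result is that "In each group (intervention and control) 130 participants will be needed". No follow-up time is attached to the 1.5 kg.
- **Effect analysis.** The outcomes at 6 and 12 months are the dependent variables, adjusted for the baseline value. "Both crude and adjusted analyses will be performed". The regression methods carry the word longitudinal in brackets. The section closes with the threshold: "For all analyses, a two-tailed significance level of < 0.05 will be considered statistically significant".
- **Discussion (abstract), Strengths and Conclusion.** Each says that the programme can be implemented directly if it proves effective. None says which result would show that.

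**The concern.** The plan is not silent on error control. It fixes one threshold for every analysis, so the family of primary tests is left unadjusted by an explicit rule. The sample size, in contrast, spends the whole 5% on a single comparison of body weight. The two sections do not describe the same trial: one has a single decisive comparison, the other has up to six outcome-by-time results, each in two models, with equal standing.

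Two things are at stake. First, a favourable conclusion could rest on whichever outcome, time point or model crosses 0.05, for example waist circumference at 6 months in one model while body weight at 12 months shows nothing. The text as written would allow that. Second, the stated 80% power covers body weight only, at a time that is not named. It says nothing about waist circumference.

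**Working it through.** **1. Reproduce the stated sample size.** Inputs from Power calculation: difference 1.5 kg, SD 4.3 kg, two-sided alpha 0.05, power 0.80.

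n per group = 2 × (1.960 + 0.842)² × (4.3/1.5)² = 129.0007, rounded up to 130. This matches. For the total, 260/0.80 = 325 against the stated 324, a rounding difference.

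Power at n = 130: the standardised difference is (1.5/4.3) × √(130/2) = 2.812. The normal approximation gives Φ(2.812 − 1.960) = 80.3%, and the t distribution gives 80.0%. The sample size is correct for one test of body weight at 0.05.

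**2. Count the primary tests.** Three outcomes × two follow-ups = 6, or 12 if both models count. Under independence the chance of at least one p < 0.05 would be 1 − 0.95⁶ = 26.5% or 1 − 0.95¹² = 46.0%. These are only upper reference points, since the tests are strongly correlated.

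**3. Allow for correlation.** The document gives no correlations, so these are assumptions:

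- weight–BMI 0.98 (adult height is fixed, so BMI is almost a rescaling of weight);
- weight–waist and BMI–waist 0.5 to 0.9;
- 6–12 months 0.5 to 0.85.

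I drew correlated standard normal test statistics with no true effect on anything and counted draws with any |z| > 1.96 (1,000,000 draws per cell).

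| Weight–waist | One effect per outcome (3 tests) | 6–12 months 0.5 (6 tests) | 0.7 | 0.85 |
|---|---|---|---|---|
| 0.5 | 9.9% | 17.5% | 16.1% | 14.5% |
| 0.6 | 9.5% | 16.9% | 15.5% | 14.0% |
| 0.8 | 8.5% | 15.1% | 13.9% | 12.4% |
| 0.9 | 7.6% | 13.6% | 12.6% | 11.2% |

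Separate tests at two follow-ups therefore give about 11% to 17%. One overall effect per outcome gives about 8% to 10%.

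**4. See what drives the excess.**

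- *BMI.* Dropping it (weight and waist, two times) gives 10.4% to 16.1% over the same grid. BMI adds about one percentage point.
- *Second model.* If crude and adjusted statistics correlate at 0.99, all twelve tests give 12.5% to 19.6% (400,000 draws per cell), which is 1 to 2 points more than six. At a correlation of 0.9 the range is 15.2% to 23.6%. Two models fitted to the same outcome in the same people, both containing the baseline value, should lie nearer the first figure.
- *Weight alone at two follow-ups.* 7.4% to 9.1%.

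The second time point and waist circumference do most of the work.

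**5. The cost of adjusting instead of choosing.** Bonferroni over four tests (weight and waist, two times) sets alpha at 0.0125. Power for weight at n = 130 is then Φ(2.812 − 2.498) = 62.4%, or 61.7% with the t distribution, against 80%.

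**The case against.** Several points can fairly be made in the plan's defence.

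- **The number of tests is not settled.** The bracketed longitudinal could mean one overall effect per outcome. That reading is plausible, and under it the error is about 8% to 10%. The text does not say that this replaces the results by time point, so both readings have to be shown. Both exceed 5%.
- **No rule says that any one significant result counts.** True. The remarks on direct implementation are discussion language, not a decision criterion. The figures are conditional on that reading, which the document neither states nor excludes.
- **Body weight is already singled out by the sample size.** In part. A reader who takes weight as the lead outcome still has two time points, and the outcome section does not rank the three.
- **A testing hierarchy may sit in an analysis plan that is not shown.** That would answer mere silence. Here the article itself applies 0.05 to all analyses, sizes one outcome and labels three as primary. Those statements need reconciling wherever the detail is kept.

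A stronger reading is tempting: that the false-positive rate is simply three times the stated 5%, or 19% to 24% once both models are counted. The document does not support this as a flat statement. A factor of about three holds for six separate tests at moderate assumed correlations and shrinks as these rise. It drops to about two if there is one longitudinal effect per outcome. The 19% to 24% figure needs a crude–adjusted correlation as low as 0.9.

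**Conclusion.** The concern holds in a conditional form. Three outcomes are labelled primary and an unadjusted two-sided 0.05 is applied to every analysis, but only body weight is sized and no time point or model is given precedence. If any one significant primary result may be taken as success, the false-positive chance is about 11% to 17% with separate tests at 6 and 12 months, or about 8% to 10% with one overall effect per outcome. The size rests on the assumed correlations listed above and on that reading of success. That it exceeds 5% does not depend on the particular correlations in the ranges.

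The sample size for body weight is sound. Severity: should be fixed before results are seen.

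**What to change.** In Effect analysis, name one primary analysis: body weight, which is the outcome the sample size supports, from the baseline-adjusted regression at two-sided 0.05. State whether it is assessed at one time point or as one overall longitudinal effect, and fix that before results are seen.

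The choice of time point belongs to the investigators. Twelve months matches the horizon of the trial and the economic evaluation. Six months matches the end of the intervention period and is also defensible. Power calculation should name the same time point.

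For the rest:

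- report BMI descriptively, as a rescaling of weight;
- treat waist circumference and the other time point as secondary, or test them in a stated fixed sequence after the primary analysis;
- say which of the crude and adjusted models is the primary one, and label the other as supportive.

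This takes one paragraph and leaves n unchanged. The price is that a result on waist circumference only, or at the other time point only, could not be claimed as a primary success. If the investigators prefer to keep several primaries, they need a stated multiplicity procedure and a new sample size. With Bonferroni over three outcomes at one time point (alpha 0.0167), that is 173 per group, or 346/0.80 = 433 in total (rounded up).
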